### Ethics Approval

The trial will be conducted in accordance with the ethical guidelines in the National Statement on Ethical Conduct in Human Research (National Statement on Human Research 2007; updated in 2018). Ethics approval for this project has been granted by the Federation University Australia Human Research Ethics Committee (A19-095), and this clinical trial is registered with the Australian and New Zealand Clinical Trials Registry (12620000422921).

## Results

Recruitment began in November 2020 and was completed at the end of March 2022. In total, 240 individuals registered for the clinical trial, of which 113 (47.1%) were assessed as eligible to commence the dMH intervention. At week 3, of the 113 participants, 73 (64.6%) met the stepped care criteria to have the dMH intervention augmented with therapist assistance, whereas 40 (35.4%) remained in the program-only condition. The results of the clinical trial are forthcoming as they have recently been accepted for publication in JMIR Publications [27].

Data will be entered, screened, and analyzed using statistical software. Intention-to-treat analysis will be used for primary outcomes, controlling for baseline differences where appropriate. The primary analysis will be conducted using 2 planned contrasts comparing a change in anxiety (GAD-7) and depression (PHQ-9) scores from preintervention assessment with those of the postintervention (week 9) and follow-up (week 21) assessments, using a mixed model repeated-measure analysis. A mixed model repeated-measure analysis is preferred owing to its ability to include participants with missing data. The study will also investigate whether reliable and clinically significant change has been achieved for participants following the recommendations of Jacobson and Traux [28]. Moderation analyses will be used to determine the role of self-efficacy and motivation in engagement and adherence and their effects on anxiety and depression outcomes in the 3 treatment conditions, and a *t* test will be used to determine the impact of preferences and treatment allocations on attrition rates.

Data obtained from open-ended questions about intervention satisfaction questionnaires and from interview questions will be transcribed verbatim from audio recordings into text and then analyzed using protocols of thematic analysis to identify common themes. Text transcripts will be read several times to identify emerging themes. Thematic analysis allows for the identification of themes that are driven by the data, using an experiential, bottom-up approach [29]. Close analysis of the data will suggest names for the themes, which are likely to represent something of meaning to participants and therapists, with direct quotes used to further illustrate meaning. Researchers will meet throughout the analysis process to review and discuss the data.

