### Participant Measures

#### Overview

Eligible participants will be given access to the preintervention (week 0) self-report questionnaire assessment comprising a demographic questionnaire (including age, sex, relationship status, education level, alcohol and other drug use, medication use, and current and past access to mental health services). Participants will also be asked to complete a short questionnaire package at weeks 3 and 6 and outcome measures after the intervention (week 9) and at the 3-month follow-up (week 21). At week 3, participants’ questionnaire data for anxiety (GAD-7) and depression (PHQ-9) will be compared against the preintervention outcome data to assess whether the stepped care rules of the trial have been met and whether a therapist is required to be assigned to a participant. Table 1 shows the schedule and frequency of the assessments during the trial for participants.

**Table 1 table1:** Schedule of enrollment and assessments.

Concepts and measures			Preintervention period (week 0)		Midintervention period (weeks 3 and 6)		Postintervention period (week 9)		Follow-up period (week 21)

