#### Life Flex Program–Only Condition

The treatment in step 1 of the trial will comprise the *program-only* Life Flex treatment program, whereby participants complete the fully automated, self-help program without therapist assistance. If participants do not improve in the *program-only* condition within the first 3 weeks (ie, no change in anxiety or depression symptoms, symptoms remain in the severe range, or noncompletion of the preintervention or week 3 questionnaire) or do not engage with the program (ie, noncompletion of the introduction module or module 1), they will be randomized to augment their program with either *low* therapist assistance (ie, one 10-minute support session per week) or *high* therapist assistance (ie, one 50-minute therapy session per week), delivered via video chat technology by provisionally or generally registered psychologists. Participants who improve or engage with the Life Flex program (program only) within the first 3 weeks maintain their no therapist assistance program. Participants who remain in the *program-only* treatment condition will complete the Life Flex program on a scheduled release design, with a new module being released every week, with the exception of module 4 (participants are given 2 weeks to work through and practice module-4 content).

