### Sample Size Calculation

Only aggregate data will be used for the main analysis. Assuming a conservative medium effect (ie, GPower f[v] test=0.25), significance set at 5% (*P*=.05), and power at 80%, 98 cases are required to demonstrate statistical significance in the primary outcome measures. However, allowing for a 30% attrition rate [26], a total target sample size of 137 participants will be required.

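### For the randomised low v high comparison, change from week 0 with only conditional baseline adjustment is unbiased but wastes precision: week-0 and completed week-3 scores both precede allocation and should always be used

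*Protocol article*

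**What the plan says.** The Randomization section allocates participants to low or high intensity when they meet the step-up criteria. The Abstract and Trial Design place that check at day 15. Under Participant Measures, Overview, the week-3 GAD-7 and PHQ-9 scores "will be compared against the preintervention outcome data to assess whether the stepped care rules of the trial have been met".

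The analysis plan is in the Results section. Two planned contrasts are described as "comparing a change in anxiety (GAD-7) and depression (PHQ-9) scores from preintervention assessment with those of the postintervention (week 9"; the sentence goes on to the week-21 follow-up and names a mixed model for repeated measures, preferred because it can include participants with missing data. On adjustment the section says: "Intention-to-treat analysis will be used for primary outcomes, controlling for baseline differences where appropriate". It names neither the covariate nor the occasion.

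Two lists of step-up criteria bear on who is randomised. The Life Flex Program–Only Condition section includes "noncompletion of the preintervention or week 3 questionnaire". The Trial Design section lists only an outstanding week-3 questionnaire.

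The Results section reports that 73 of 113 participants met the step-up criteria. It does not give the split between low and high.

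**The concern.** Low v high is the only randomised comparison in the trial. For anyone stepped up on scores, both the week-0 and the week-3 values were recorded before allocation, yet the article classes week 3 as a mid-intervention assessment and states no use for it as a pre-randomisation value. A change score gives the week-0 value a fixed weight of one, which is more than its correlation with the outcome warrants, and leaves the more recent value unused. Adjustment that applies only in some circumstances also leaves the primary model open at the point where it should be closed.

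What is at stake is precision. The Discussion says that if low and high give similar outcomes, this will support implementing low-intensity interventions. In a comparison of at most 73 people, avoidable noise makes a real difference easier to mistake for similarity.

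**Working it through.** **1. The plan's own figure.** Inputs from Sample Size Calculation: "Assuming a conservative medium effect (ie, GPower f[v] test=0.25"), a 5% significance level, and "power at 80%, 98 cases are required to demonstrate statistical significance in the primary outcome measures". Take the G*Power repeated-measures MANOVA, within-between interaction, with k groups and m occasions: s = min(k−1, m−1), λ = N·s·f(V)², df1 = (k−1)(m−1), df2 = s(N − k − (m−1) + s). With k = 3, m = 3 and N = 98:

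- λ = 98 × 2 × 0.0625 = 12.25
- df1 = 4; df2 = 2 × (98 − 3 − 2 + 2) = 190
- power = 0.8005, so 98 is reproduced exactly.

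The target of 137 is 98 × 1.4 = 137.2. Three occasions fit weeks 0, 9 and 21. Four occasions would need 113 and the five collected would need 125. This suggests, without proving it, that week 3 had no part in the planned test.

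**2. Relative variance of the low v high difference at week 9.** Assume equal variances and a common correlation r between weeks 0, 3 and 9:

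- change from week 0: 2(1 − r)
- adjusted for week 0: 1 − r²
- adjusted for weeks 0 and 3: 1 − 2r²/(1 + r)

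| r (assumed) | Change | Week 0 | Weeks 0 and 3 | Week 0 v change | Adding week 3 | Total v change |
|---|---|---|---|---|---|---|
| 0.5 | 1.00 | 0.75 | 0.67 | −25% | −11% | −33% |
| 0.6 | 0.80 | 0.64 | 0.55 | −20% | −14% | −31% |
| 0.7 | 0.60 | 0.51 | 0.42 | −15% | −17% | −29% |

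The total is worth about 1/0.71 to 1/0.67, that is 1.4 to 1.5 times as many participants with both scores.

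**3. Unequal correlations, in terms of power.** Assume r03 = 0.6, r09 = 0.5, r39 = 0.6, a true difference of 0.5 SD, a 1:1 split, 30% attrition (73 × 0.7 ≈ 51, or 25.5 per arm) and a two-sided 5% test. For both scores, R² = (0.25 + 0.36 − 2 × 0.5 × 0.6 × 0.6)/(1 − 0.36) = 0.391. SE = √(variance × 2/25.5) and power = Φ(0.5/SE − 1.96).

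| Analysis | Variance | SE | Power |
|---|---|---|---|
| Change from week 0 | 1.00 | 0.280 | 43% |
| Adjusted for week 0 | 0.75 | 0.243 | 54% |
| Adjusted for week 3 | 0.64 | 0.224 | 61% |
| Adjusted for both | 0.61 | 0.219 | 63% |

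Over six correlation sets (r03 0.5–0.7, r09 0.3–0.6, r39 0.5–0.7), change from week 0 needs 1.5 to 2.0 times the participants of adjustment for both. Power is 33–51% against 54–73%.

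**4. How week 3 enters the model matters.** With complete data and the step 3 correlations, adding week 3 as one more response in an unconstrained mixed model leaves the SE of the week 0-to-9 contrast at 0.280. Holding the week-0 and week-3 means equal across the arms brings it to 0.219.

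**5. Missing scores.** Same correlations, with the missing fractions assumed:

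- 10% missing week 0: SE 0.291 in the unconstrained mixed model, against 0.295 if those participants are dropped and 0.246 with a common week-0 mean.
- 30% missing week 3, week 0 complete: SE 0.225 with common week-0 and week-3 means, against 0.280 for change from week 0.

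**The case against.** Several stronger readings are tempting, and the document does not support them.

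- *Week 0 is an invalid reference.* It is not. Week 0 precedes allocation, so change from week 0 is unbiased for low v high. It is also the baseline that all three conditions share.
- *Week 3 is discarded.* The Results section names the contrasts, not every occasion in the model. The match to three occasions is indirect evidence only.
- *Participants without week 0 cannot be analysed.* With week 0 as a response, change is a contrast of model means and no individual change score is needed; the article chose the mixed model for its handling of missing data. They would be lost only if change were the dependent variable or week 0 a required covariate. Whether such people are randomised at all is unclear, since the two step-up lists disagree.
- *Covariates will be picked after looking at imbalance.* The clause allows this, but names no test or selection rule.

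Three further objections carry weight. First, this is a condensed article, and covariate lists are commonly left to an analysis plan. That would excuse silence, but the article states a rule and makes it conditional. Second, the 29–33% combines two changes: ordinary week-0 adjustment, for which the clause leaves room, supplies the larger part at correlations of 0.5 and 0.6. Third, a missing week-3 questionnaire is itself a step-up criterion, so the full gain does not reach everyone randomised. Step 5 shows that most of it survives 30% missing.

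**Conclusion.** The point holds as one of efficiency and prespecification in the low v high comparison, not of validity. Against change scores, using both pre-randomisation values lowers the variance by about 29–33% under a common correlation of 0.5 to 0.7. Week 3 contributes an 11–17% reduction beyond week-0 adjustment. In the central unequal-correlation case, power for a 0.5 SD difference rises from 43% to 63%.

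The loss appears at every correlation set tried, but its size rests on assumed correlations, a 1:1 split, 30% attrition applied to the 73, and the 0.5 SD difference. The document gives no correlations, and the randomised group is selected partly on these same scores.

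A reader might infer that the same change would also strengthen the comparison of therapist assistance with program only. It would not: that comparison is not randomised, and week-3 scores help to decide who is in which group.

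**What to change.** For low v high, replace the conditional adjustment clause with a fixed rule. Always use the week-0 scores, and the week-3 scores completed before allocation, as pre-randomisation values of GAD-7 and PHQ-9. One sound form is a mixed model with both as responses, their means constrained equal across the two arms, and the arms contrasted at weeks 9 and 21; it keeps participants who lack either score. Covariate adjustment with a stated rule for missing values is an alternative. A week-3 questionnaire completed after allocation must not be treated as a pre-randomisation value.

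Reconcile the step-up lists in Trial Design and Life Flex Program–Only Condition on whether a missing preintervention questionnaire leads to randomisation, and report how many entered by that route.

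The cost is model specification and a rerun, because data collection is complete. As the article says the results are already accepted for publication, present this as a labelled re-analysis beside the published one, not as the prespecified primary analysis.

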### Objectives

The purpose of this study is to present a protocol designed to evaluate various support intensities of a dMH treatment program for anxiety and depression within a mixed methods design. Therefore, the study has the following primary objectives:

To compare the efficacy of clinical outcomes (anxiety [Generalized Anxiety Disorder–7; GAD-7] and depression [Patient Health Questionnaire–9; PHQ-9] symptoms) among the 3 treatment conditions (dMH program only, low-intensity therapist assistance, and high-intensity therapist assistance), with particular focus on whether therapist-assisted support produces greater reductions in anxiety and depression severity compared with those produced by dMH program–only support.To examine the role of motivation and self-efficacy on engagement, adherence, and clinical outcomes (anxiety [GAD-7] and depression [PHQ-9] symptoms) among the 3 treatment conditions (dMH program only, low-intensity therapist assistance, and high-intensity therapist assistance) at postintervention (week 9) and follow-up (week 21) assessments, compared with those at preintervention (week 0) assessment.To explore participant and therapist experiences and satisfaction with assessment and therapist assistance delivered via video chat technology, using semistructured interviews; specific areas of focus will include the ability to develop and maintain therapeutic relationships, implementation barriers and facilitators, and identified strengths and limitations of video chat technology for conducting assessments and delivering dMH treatment.To explore therapist training and implementation experiences in the delivery of dMH interventions.To use a mixed methods analysis to examine factors affecting participant attrition in each of the treatment intensities; quantitative examination of preferences, treatment condition allocation (dMH program only, low-intensity therapist assistance, and high-intensity therapist assistance), and attrition rates will be explored; qualitative exploration of participant reasons for withdrawal and nonengagement with therapist support will also be conducted using semistructured interviews.To explore the outcomes of working alliance, health resources, and health status among the 3 treatment conditions (dMH program only, low-intensity therapist assistance, and high-intensity therapist assistance).

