## Methods

### Trial Design

This trial will follow the International CONSORT (Consolidated Standards of Reporting Trials) guidelines and evaluate the conditions using an adaptive randomized clinical trial design [12]. The clinical trial also adheres to SPIRIT (Standard Protocol Items: Recommendations for Interventional Trials; Multimedia Appendix 1). All information will be strictly confidential, yet subject to legal limitations (eg, legal subpoena), and only accessed by the investigators. Data are stored securely using 256-bit encryption Secure Sockets Layer and Transport Layer Security software when information is transmitted. Any hard copy data will be stored securely in lockable filing cabinets at the Federation Community Psychology Services at Federation University.

Eligible participants will be given access to a self-help dMH treatment program (Life Flex) and have their symptoms of anxiety or depression evaluated at day 15 to assess whether they meet the criteria to have their treatment program augmented with therapist assistance. Participants will be considered as eligible to be *stepped up* to a therapist-assisted condition if they meet any of the following criteria: they have not read the introduction module or module 1 of the Life Flex program; have symptoms of anxiety or depression that have deteriorated by >5 points (as assessed by comparison of their baseline depression [PHQ-9] and anxiety [GAD-7] scores against their week-3 scores); show symptom improvement, but their scores remain in a severe range; and are yet to complete the week-3 questionnaire assessment.

Outcomes will be assessed before the intervention (week 0), during the intervention (weeks 3 and 6), after the intervention (week 9), and at the 3-month follow-up (week 21). Results will be disseminated via publication. Figure 1 illustrates the study’s design and expected participant flowchart.

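### The role of motivation and self-efficacy in engagement is to be examined across three conditions that are formed in part by early engagement and early symptom response

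*Protocol article*

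**What the plan says.** The second item under Objectives is "To examine the role of motivation and self-efficacy on engagement, adherence, and clinical outcomes", among program-only, low-intensity and high-intensity assistance. The matching sentence in the Results section reads "Moderation analyses will be used to determine the role of self-efficacy and motivation in engagement and adherence", and goes on to "their effects on anxiety and depression outcomes in the 3 treatment conditions".

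Condition is decided at day 15. Under Trial Design, any one of several criteria makes a participant eligible for step-up:

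- Early engagement: "they have not read the introduction module or module 1 of the Life Flex program".
- Assessment completion: they "are yet to complete the week-3 questionnaire assessment".
- Symptoms: deterioration of more than 5 points, or they "show symptom improvement, but their scores remain in a severe range".

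Life Flex Program–Only Condition restates the engagement rule: participants who "do not engage with the program (ie, noncompletion of the introduction module or module 1), they will be randomized to augment their program". Under Randomization, only low versus high is allocated at random, and only once the step-up criteria are met. Results reports 113 starters, of whom 73 were stepped up and 40 stayed in program-only.

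**The concern.** A model in which condition moderates the link between motivation and engagement needs condition not to be a consequence of that same link. Here it can be. If motivation drives early module use, and early module use decides who leaves program-only, then program-only holds participants selected for adequate early engagement, and the therapist arms collect those without it. Selecting on an outcome narrows its range and changes its slope on any predictor. The narrowing differs between the groups, so slopes can differ when support has no effect on them. The symptom criteria add to this, because anxiety and depression are outcomes of the same objective.

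Two readings are at risk. One is that motivation matters little in self-help, read from a flattened program-only slope. The other is that motivation matters more once a therapist is involved, read from a slope difference that group formation produced. Principal Findings intends this analysis to improve understanding of attrition and engagement in digital interventions. The Limitations section does not mention the selection.

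**Working it through.** **Reported counts.** 73/113 = 64.6% and 40/113 = 35.4%, as the Results section states. The protocol gives no figure for the association itself, so what follows illustrates direction and range. It does not estimate this trial's bias.

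**Illustration 1: engagement rule plus other reasons.**

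- Assumed inputs: motivation M, early engagement E and later engagement L are trivariate normal, with corr(M,E) = corr(M,L) = 0.4 and corr(E,L) = 0.7. The lowest 30% to 64.6% on E are stepped up by the engagement rule. A random remainder brings the stepped-up total to 64.6%. There is no effect of condition. 2 million draws per scenario.
- Whole sample, total engagement T = E + L: corr(M,T) = (0.4 + 0.4)/√(2 + 2 × 0.7) = 0.8/√3.4 = 0.43.

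| Share of all starters stepped up by the engagement rule | corr(M,T), program-only | corr(M,T), stepped up | Slope of standardized T on M, program-only | Slope, stepped up |
|---|---|---|---|---|
| 30% | 0.34 | 0.44 | 0.27 | 0.45 |
| 64.6% (all 73) | 0.29 | 0.33 | 0.19 | 0.25 |

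The whole-sample slope is also 0.43. In the first row the stepped-up slope exceeds the program-only slope by 0.45 − 0.27 = 0.18 with no true moderation. Counting only later engagement does not remove the effect: corr(M,L) is 0.27 to 0.31 in program-only against a true 0.40. When corr(M,E) = corr(M,L) is varied over 0.3 to 0.5 and corr(E,L) over 0.5 to 0.7, mean total engagement differs between the groups by 0.7 to 1.5 SD.

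**Illustration 2: how strongly engagement drives step-up.**

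- Engagement E = bM + √(1 − b²) × noise. Step-up index I = wE + √(1 − w²) × noise. The lowest 64.6% on I are stepped up. The true slope b is 0.30 (0.299 in the draws).

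| w | Slope, stepped up | Slope, program-only |
|---|---|---|
| 1.0 | 0.143 | 0.093 |
| 0.7 | 0.225 | 0.201 |
| 0.5 | 0.262 | 0.251 |
| 0.3 | 0.287 | 0.281 |

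At w = 0.3 the loss is 1 − 0.287/0.299 = 4% in stepped-up participants and 1 − 0.281/0.299 = 6% in program-only. At w = 1.0 it exceeds half in both groups. An analysis of all starters that ignores condition recovers b.

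**Precision of the randomized comparison.** With 73 participants split 36 and 37 (assumed, no attrition), the standard error of a difference between two correlations on Fisher's z scale is √(1/33 + 1/34) = 0.24. The 95% half-width is 1.96 × 0.24 = 0.48.

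**The case against.** **The analysis may be pooled.** The Results section gives one condensed sentence, and its phrase about three conditions is attached to the symptom outcomes. The engagement part could be read as pooled over conditions. The Objectives do not allow that reading, because they place engagement and adherence among the three conditions. It is true that no section defines the engagement measure or its time window. One might infer that engagement will be counted over the whole program, days 1 to 15 included; the protocol does not say so. The distortion does not depend on it, since later engagement alone is affected too.

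**Engagement is only one criterion.** A reader might infer that the conditions are defined by early engagement, or that everyone left in program-only is an engager. The first is too strong, because symptom criteria also step people up. The second follows from the any-criterion rule under Trial Design, but Life Flex Program–Only Condition keeps those who improve or engage, which could include a non-engaging improver. The two passages need to be reconciled.

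**The size is assumed.** This stands. The protocol does not say how many of the 73 failed the engagement rule. At the 30% end, stepped-up participants show no attenuation (0.44 against 0.43). In simulated trials of 40 versus 73 with no true moderation, a condition-by-motivation interaction was significant at the 5% level in about 5 to 23% of trials, depending on the inputs. A false moderation finding is more likely than it should be, but it is not the expected result.

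**It is secondary and derivative.** The root is that program-only is a non-randomized, response-selected group. The Abstract and Principal Findings call this objective secondary, although Objectives lists it under the primary ones. That limits the weight of the point. It does not remove it, because this question has its own remedy.

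**Conclusion.** The concern holds in a limited form. As stated, the plan examines engagement, adherence and symptoms across groups formed in part by early engagement and early symptom response. Slopes within program-only, and slope differences between program-only and the therapist arms, can reflect selection and be mistaken for moderation by support. Moderation within low versus high remains internally valid, though it applies only to stepped-up participants.

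The size is unknown. It ranges from about 4 to 6% attenuation, if engagement drives step-up weakly, to more than half, if engagement alone drives it. These figures rest on assumed normal variables and assumed correlations. A reader might conclude that the analysis will understate the role of motivation by a known amount, or will report a spurious therapist effect. The protocol supports only that it could.

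**What to change.** 1. Relate week-0 motivation (CMOTS) and self-efficacy (BPSES) to engagement before step-up, in all starters with week-0 data. Everyone receives the same program in that period. The number is at most 113: Life Flex Program–Only Condition lists non-completion of the preintervention questionnaire among its step-up reasons, so some starters may lack these scores. Report how many, since they may be the least engaged.
2. Test moderation by support intensity only in low versus high (73 participants). Count engagement and adherence from randomization, and use symptom scores taken after it. Use week-0 CMOTS and BPSES as the moderators. Report the estimate with its confidence interval.
3. Describe engagement in program-only without comparing its slope with the therapist arms, and add the selection to Limitations.

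**Cost.** The three-condition moderation claim is given up. The low versus high test is imprecise, as the half-width of 0.48 shows, so absence of moderation could not be concluded from it. Days 1 to 15 cover few modules, so the first analysis has a coarse engagement measure and says nothing about adherence over the whole program. Module reading has to be tracked to apply the step-up rule, so the data probably exist, but the protocol does not describe them. Collection is complete and the trial results are accepted elsewhere, so in practice this means re-specifying and relabelling a secondary analysis.

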#### Preferences

A bespoke preferences questionnaire has been purposively developed to assess participants’ preferences for treatment before commencing the trial. Participants are presented with brief information about each of the 3 treatment conditions (dMH program only, low intensity therapist assistance, and high intensity therapist assistance), which they are then asked to rank in order of their preference.

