### Randomization

The process of randomly allocating participants to either the low-intensity or high-intensity treatment groups will comply with CONSORT guidelines. A block randomization design will be used to randomly allocate each participant to either the low-intensity or high-intensity therapist assistance condition throughout the trial. Random allocation will occur when a participant has met the criteria to be *stepped up* to have their Life Flex program augmented with therapist assistance. Participants will be aware of the group they have been randomly allocated to but will remain unaware of the study’s objectives. The provisional or general psychologists will not be blinded to the treatment conditions, as they will need to adhere to either the support or the therapist role.

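### A t test does not fit an attrition objective with three conditions and a ranked preference, and the step-up rule selects the program-only group on early engagement

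*Protocol article*

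**What the plan says.** The analysis paragraph in the Results section of the protocol article states that a t "test will be used to determine the impact of preferences and treatment allocations on attrition rates".

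The Objectives section sets the question that this test is meant to answer: "quantitative examination of preferences, treatment condition allocation (dMH program only, low-intensity therapist assistance, and high-intensity therapist assistance), and attrition rates will be explored". The Preferences section describes a questionnaire that presents the three conditions, "which they are then asked to rank in order of their preference".

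Membership of the conditions is fixed by two rules:

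- **Step-up.** Under Trial Design, participants qualify "if they meet any of the following criteria", one of which is that they "are yet to complete the week-3 questionnaire assessment". The section on the Life Flex Program–Only Condition repeats this as "noncompletion of the preintervention or week 3 questionnaire" and adds "noncompletion of the introduction module or module 1". A later sentence in that section keeps participants who improve or engage in program only.
- **Randomisation.** "A block randomization design will be used to randomly allocate each participant to either the low-intensity or high-intensity therapist assistance condition". Program only is not a randomised arm.

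The Results section reports that 73 of 113 starters met the step-up criteria and 40 stayed in program only.

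**The concern.** There are two separate problems.

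The first is the test. A t test compares two means. It cannot compare three conditions in one step, it cannot take a ranking of three options as its grouping factor, and it cannot estimate the effects of allocation and preference together. The article states no recoding that would reduce either factor to two groups.

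The second is the comparison. Failing to complete the week-3 questionnaire, or to engage with the early modules, is an early sign of dropout. The step-up rule uses these same signs to move people out of program only. The program-only group is thus selected for early engagement, and the therapist arms receive those who had not engaged. A reader of the finished analysis could conclude that adding a therapist, or receiving a non-preferred condition, worsens retention when the rule itself produced some or all of the difference.

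What is at stake is the attrition objective. The GAD-7 and PHQ-9 analyses do not use this test.

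**Working it through.** **Plan's own figures.** 73/113 = 64.6% and 40/113 = 35.4%, as stated. 73 + 40 = 113, so all starters are in one of the two groups and no third group holds early losses.

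**Step 1: the test against the factors.** Allocation has three levels (Objectives). Preference is an ordering of three options (Preferences), which means three possible first choices and 3! = 6 possible rankings. A t test takes one factor with two levels. Covering allocation alone with pairwise t tests needs three of them. At 0.05 each, and treated as independent, the familywise error is 1 − 0.95³ = 0.143, about 14%.

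**Step 2: does a yes/no outcome matter in itself?** A simulation of 40,000 runs applied a two-group t test to a yes/no outcome with 30% attrition in both groups. It rejected in 5.0% of runs at 40 versus 73, and in 4.8% at 36 versus 37 (an assumed near-equal split of the 73). The nominal level is 5%, so this aspect is minor.

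**Step 3: what the step-up rule does to the comparison.** The 30% attrition rate is the planning figure from the Sample Size Calculation. Three assumptions are added: a share *s* of all attrition falls before week 3; everyone lost before week 3 is among the 73 stepped up, as the criteria read literally; and the risk after week 3 is the same in both groups. Then:

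- early losses: E = 113 × 0.30 × s
- later losses: L = 113 × 0.30 − E
- risk after week 3: q = L / (113 − E)
- program-only attrition = q
- stepped-up attrition = [E + q × (73 − E)] / 73

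Worked for s = 1/3: E = 11.3, L = 33.9 − 11.3 = 22.6, q = 22.6/101.7 = 22.2%. Stepped-up attrition = (11.3 + 0.222 × 61.7)/73 = 25.0/73 = 34.3%.

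| Share before week 3 (assumed) | E | Program only | Stepped up | t test rejects |
|---|---|---|---|---|
| 0 | 0 | 30.0% | 30.0% | 5% |
| 1/3 | 11.3 | 22.2% | 34.3% | about 24% |
| 1/2 | 16.9 | 17.6% | 36.8% | about 60% |
| 2/3 | 22.6 | 12.5% | 39.6% | about 94% |

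The last column is from 40,000 simulated runs per row, with E rounded to a whole number. Later risk is equal by construction, so every difference in the table comes from the allocation rule.

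**The case against.** Several points on the other side carry weight.

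- **A t test is not useless here.** It could compare randomised low with high, or matched with unmatched preference, and a condensed article may leave the coding to a fuller plan. This stands in part. But the article names the test and also names three conditions for the same objective, so the mismatch is in what it says. Matched versus unmatched would give two groups, but whether someone can match program only depends on their own early engagement and symptoms.
- **The yes/no outcome.** A reader might infer that a t test on dropout is invalid because dropout is binary. The documents do not support making that the main fault: attrition is nowhere defined, and on the natural yes/no reading the test keeps its size (Step 2).
- **Is early retention in program only guaranteed?** A reader might infer that program-only attrition up to week 3 is zero by construction. That goes too far. The assessment is at day 15, and someone whose questionnaire is outstanding then may complete it later. The criteria make people eligible for step-up, and the sentence keeping those who improve or engage in program only could retain an engaged participant who has not completed the questionnaire. Selection on early engagement stands; a guarantee does not.
- **Size.** A reader might want to say what fraction of the 73 were already disengaging. Step-up reasons are not reported, so any such count would be invented.
- **Importance.** The objective is exploratory. This limits the weight of the point but does not remove it.

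**Conclusion.** The point holds in a limited form. The named test does not fit an objective with three conditions and a ranked preference. Any attrition contrast with program only is biased in favour of program only, provided that those stepped up for non-completion or non-engagement go on to drop out more often than others.

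The size of that bias is unknown. In the illustration it runs from no difference (no attrition before week 3) to 12.5% versus 39.6% (two thirds before week 3). This rests on 30% total attrition, equal later risk, and all early losses falling in the stepped-up group. If late completers mostly stay, the bias is towards the small end.

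The analysis should be changed. The consequence is confined to the attrition objective.

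**What to change.** 1. **Define attrition** as dropout by week 9, and separately by week 21.
2. **Test only the randomised comparison.** Compare low with high by a Fisher test, or by a small penalised logistic regression on arm and preference, and report odds ratios with confidence intervals. Code preference either as first-ranked condition or as match with the allocated condition, and state which. Within these two arms anyone who ranked program only first is always unmatched, so a match effect cannot be separated from that preference.
3. **Report program-only attrition after week 3 descriptively**, without a causal test against the therapist arms.
4. **Reconcile the passages.** The sentence keeping those who improve or engage in program only must be squared with the step-up criteria under Trial Design and in the program-only section, so that it is clear who could be in each group.

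Cost: one analysis is replaced and no new measurements are needed. The model has to stay small. At 30% attrition, 0.30 × 73 = 21.9, so about 22 dropouts are expected in the two randomised arms. Arm plus match uses two parameters (22/2 = 11 dropouts each); arm plus first-ranked condition uses three (22/3, about 7 each). Step-up reasons overlap and would overload the model. The article reports that data collection is complete and that results have been accepted for publication, so if the data have already been analysed the new analysis should be labelled post hoc.
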